### User Involvement

The users, in our case Norwegian elementary and junior high school students, have been involved in the project from the development of the intervention to its evaluation. The app was developed in collaboration with the users in terms of what the intervention should contain, but also in terms of functionality and format of the app. The 8 adolescents in the user group were involved through workshops. A larger reference group consisted of teachers, school health nurses, nurses from the health care station for adolescents, community psychologists, and the local antibullying professional.

The aim of the current paper is to provide a description of the content of the intervention and the randomized controlled trial that will be conducted to examine the effectiveness of NettOpp.

## Methods

### Eligibility Criteria and Setting of the Effectiveness Study

Adolescents from the 6th to 10th grade (11-16 years old) are eligible for participation in the effectiveness study. Adolescents will be recruited through schools in Norway. To recruit enough participants, the schools need to be big enough; that is, they should have at least 20 students in each class.

### Inclusion and Exclusion Criteria

Adolescents between the ages of 11 and 16 years, whose guardians have given consent and who agree to take part in the study, will be included. To use the app, adolescents need a smartphone and be able to read and understand Norwegian. Furthermore, android users must provide a Gmail address, and iPhone users must first download the free app TestFlight to be able to download a test version of NettOpp. Adolescents who may not benefit from an app-based intervention because of, for example, severe developmental or cognitive challenges will be excluded from the study.

### Intervention

NettOpp is a self-help tool that aims at supporting adolescents who have been exposed to cyberbullying or a negative online event. Adolescents can install the app on their mobile phone and use it as much as they want and whenever they want. The intervention focuses on psychoeducation, on motivating the adolescents to seek help from a trusted adult, and on strategies to better cope with stress related to cyberbullying or negative online experiences.

### Control

The waiting-list control group will receive access to the app after study completion; that is, when the follow-up assessment is conducted after approximately 3 months.

### Randomization

The effectiveness study will be conducted as a randomized controlled trial with an intervention group and a waiting-list control group. Randomization will be conducted after baseline measures have been collected at the school level by a statistician. A random number between 0 and 1 will be generated using SPSS and assigned to each school. Half of the schools with the highest value on the random variable will be assigned to the intervention group and half of the schools with the lowest value will be assigned to the waiting-list control group.

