## Introduction

### Background

The technological revolution has led to most young people being able to now use the internet and mobile phones daily to communicate with others, socialize, entertain themselves, and find information. This development goes hand in hand with many new challenges and possibilities also when it comes to aversive behavior among children and youth. On the one hand, cyberbullying and other negative online experiences affect many children and youth. On the other hand, this technological development opens up for new innovative technologies to help and support young people exposed to such behavior.

Cyberbullying can be defined as an “aggressive, intentional act carried out by a group or individual, *using electronic forms of contact*, repeatedly and over time against a victim who cannot easily defend him or herself” [1]. Electronic forms can be the internet and other digital technologies including mobile phones that are used to, for example, call, write emails, instant, and text messages, chats, blogs, or web posts to say mean things, insult, threaten, or make fun of somebody, to spread rumors, lies, embarrassing information, or pictures [2]. Cyberbullying can take on many different forms, from passively ignoring or excluding somebody from a group to more active actions such as sending or posting cruel or embarrassing messages about someone [2,3].

Cyberbullying prevalence rates among 12-to-18-year-old individuals vary from 5% to 74% with a median of 23%, as reported in a review by Hamm et al [4]. Some of this variation can probably be explained by age group and country differences in the prevalence of cyberbullying. Nonetheless, we believe it is likely that this huge variation is also due to the use of different definitions, perceptions, and interpretation for cyberbullying across studies; that is, does cyberbullying have to occur repeatedly or is one occurrence enough [3-6] and what are the different types of scales used to measure the phenomenon? The annual conducted Norwegian school survey among 10-to-18-year-old students reported a cyberbullying rate of 2% in 2017 with a peak (2.6%) in junior high school [7]. This is the proportion of adolescents who report that they have been cyberbullied 2-3 times a month or more. The proportion increases to 10% if adolescents who have experienced one negative online event are included.

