### The Cyberbullying Coping Intervention

NettOpp is a mobile app for adolescents who have been exposed to cyberbullying or other negative online experiences in Norway (Figure 1). NettOpp directly translated means “exactly” in English but “Nett” refers also to the internet and “Opp” comes from “Opplysning,” which means information or enlightenment. The target group of the cyberbullying coping intervention was adolescents in elementary school and junior high school, between 11 to 16 years of age. According to Jacobs et al [22] (2014), a cyberbullying coping intervention should do more than just increase awareness about internet threats. Ideally, an intervention should reduce the risks for getting victimized, combat cyberbullying once it occurred, and buffer the negative impact of the event [23].

The primary aim of this intervention is (1) to reduce mental health problems related to cyberbullying; the secondary aims are to (2) increase adolescents coping skills with cyberbullying, (3) increase knowledge about cyberbullying, (4) increase the help-seeking behavior of the adolescents, (5) increase their self-esteem, (6) increase their sleeping quality, and finally, (7) reduce cyberbullying. Below a description of why it is important to focus on the aforementioned aims.

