### Power Calculations

Power calculations were conducted using the software PASS 16 [53]. Using multilevel analysis, it will require a total sample of 400 participants (200 in each group: 20 schools with 20 students per group) to detect an effect size of at least Cohen *d*=0.30, when the expected interclass correlation at school level is 0.01, with a power of 0.79, and a significance level of .05.

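### About 20 schools of two types are allocated by one unstratified random sort; running the same draw within school type would remove avoidable chance imbalance at almost no cost

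*Protocol article*

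**What the plan says.** All references are to the protocol article.

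- **Randomization** gives the whole procedure. On timing and unit: "Randomization will be conducted after baseline measures have been collected at the school level by a statistician". On method: "A random number between 0 and 1 will be generated using SPSS and assigned to each school". On the split: "Half of the schools with the highest value on the random variable will be assigned to the intervention group", with the lower half going to the waiting list. No strata, pairing or balance constraint is named, and a single ranking of all schools leaves no place for one.
- **The Cyberbullying Coping Intervention** describes the target group as "adolescents in elementary school and junior high school, between 11 to 16 years of age". The eligibility section admits grades 6 to 10.
- **Power Calculations** states "it will require a total sample of 400 participants", described as "200 in each group: 20 schools with 20 students per group", "to detect an effect size of at least Cohen *d*=0.30", with a school-level ICC of 0.01, power 0.79 and significance level .05.
- **Planned Statistical Analysis** names a linear mixed model. No covariates are listed, which is normal for an article.

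**The concern.** With few randomised units, a simple split can by chance place clearly more schools of one type in one arm. School type goes with age and may go with the level of the outcomes. The allocation method is fixed in the article, so it is not a detail left for an analysis plan, and balance cannot be restored once the draw is made. At stake is either a chance shift in an unadjusted contrast or, if type is adjusted for, a loss of precision in a trial planned at 0.79 power. Allocation after baseline means that the information needed to avoid this is already available.

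**Working it through.** **1. Number of schools.** The wording in Power Calculations can be read as 20 schools in total or 20 per group. The stated power shows which reading fits.

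- Inputs: 200 students per arm, 20 per school, ICC 0.01, d = 0.30, two-sided alpha 0.05 (sidedness is not stated).
- Design effect = 1 + (20 − 1) × 0.01 = 1.19. Effective n per arm = 200 / 1.19 = 168.1.
- Power = Φ(0.30 × √(168.1/2) − 1.96) = Φ(0.79) = 0.785, which matches the stated 0.79.
- Twenty schools per arm gives 0.820 with 10 students each or 0.973 with 20 each. Neither matches.

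So about 20 schools are randomised, 10 per arm.

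**2. Chance of imbalance.** When the ranking is cut in half, the number of schools of one type in one arm is hypergeometric. With 10 of each type:

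P(7:3 or worse) = 2 × (120² + 45² + 10² + 1²) / 184,756 = 33,052 / 184,756 = 17.9%.

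P(8:2 or worse) = 2 × (45² + 10² + 1²) / 184,756 = 2.3%.

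The documents do not give the mix, so a range is needed:

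| Schools of the less common type, of 20 (assumed) | P(between-arm gap of 4 or more) |
|---|---|
| 4 | 8.7% |
| 5 | 3.3% |
| 6 | 14.1% |
| 7 | 5.7% |
| 8 | 17.0% |
| 9 | 7.0% |
| 10 | 17.9% |

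For odd counts the gap can only be 1, 3, 5 and so on; a gap of 3 or more has probability 30% to 37%. If there were 40 schools, 20 of each type, a difference in proportions of 0.4 or more would have probability 2.6%. A draw within type gives an exact split for even strata and a gap of at most one school for odd strata.

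**3. Effect on an unadjusted contrast of levels, 10 of each type.** If the types differ by δ SD, type contributes δ²/4 to the between-school variance. An ICC of 0.01 therefore caps δ at √(4 × 0.01) = 0.20, reached only if type explains all of it. At 7:3 the difference in proportions is 0.7 − 0.3 = 0.4, so the shift is at most 0.4 × 0.20 = 0.08 SD, and 0.08 / 0.30 = 27% of the target effect. At 6:4 it is at most 0.2 × 0.20 = 0.04 SD.

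**4. Effect of adjusting for type after a 7:3 split.** The correlation between arm and type is (7 − 3)/10 = 0.4, so the variance rises by 1/(1 − 0.16) = 1.19.

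- If the ICC stays at 0.01: effective n = 168.1 × 0.84 = 141.2 and power = Φ(0.30 × √70.6 − 1.96) = 0.712, against 0.785 at 5:5.
- If type explains all of the ICC: effective n = 200 × 0.84 = 168 and power is again about 0.785, against 0.851 at 5:5.

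The 0.08 SD shift belongs to the second case and the power of 0.712 to the first. They are two ends of a range and do not occur together.

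**5. Price of the stratum term.** With a t reference, power is 0.739 on 18 df and 0.736 on 17 df, a loss of 0.3 percentage points.

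**The case against.** The strongest reply is that nothing here is an error. The sort is a valid 1:1 cluster randomisation, unbiased in expectation, and a mixed model with a school effect allows for chance differences between schools. That stands.

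Several stronger readings are tempting, and the documents do not support them:

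- **That arm is confounded with exposure to cyberbullying.** The Background section cites a survey that "reported a cyberbullying rate of 2% in 2017 with a peak (2.6%) in junior high school". The 2% covers all students aged 10 to 18, and no elementary rate is given. With an assumed elementary rate of 1.4%, a 7:3 split moves exposure by 0.4 × 1.2 = about 0.5 percentage points, one student in 200. Even at an assumed 0% it moves 0.4 × 2.6 = about 1.0 point.
- **That a level difference between school types carries straight into the result.** The primary hypothesis concerns change. A stable level difference largely drops out of a comparison of change, and the documents do not show that type predicts change.
- **That any departure from 5:5 is a hazard.** With 10 of each type, 6:4 or worse has probability 65.6%, but most of that is 6:4, where the shift is at most 0.04 SD.
- **That too few degrees of freedom remain to adjust.** A type term costs one, and age or grade can be adjusted at student level.

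The mix is also assumed: equal numbers of each type give the highest risk of a gap of 4 or more, and combined schools would blur the contrast. These points limit the size of the problem. They do not show that the simple sort does as well as a stratified one.

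**Conclusion.** The point holds as a cheap improvement to a valid design. It does not show bias in the planned comparison. About 20 schools of two types are allocated without using a factor known at the draw. The chance of a gap of 4 or more schools of one type is roughly 3% to 18%, depending on the mix. With equal numbers of each type, the consequence at 7:3 is a shift in level of at most about 0.08 SD, smaller for change, or a rise of about 19% in the variance of a type-adjusted estimate.

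This rests on 10 schools per arm (inferred from the power statement), an assumed mix of 4 to 10 of 20, equal school sizes and the stated ICC of 0.01. It also takes every school to be enrolled before the draw, which one ranking of all schools implies.

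**What to change.** Run the same SPSS draw separately within school type (elementary, junior high, and combined schools as a third stratum if there are any). Where strata have odd numbers, let chance decide which arm receives the extra school, under a rule that keeps the arm totals equal. Include school type in the mixed model. State the number of schools in Power Calculations unambiguously at the same time.

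The cost is a sentence or two in the plan, a little of the statistician's time, and one or two degrees of freedom. Recruitment, measures and participants are unaffected. The change must be made before allocation.

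Covariate-constrained randomisation on baseline scores is an optional further step. It is more demanding, because every school's baseline data would have to be cleaned and scored before the draw.

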### Blinding

Adolescents are randomized to the intervention or waiting-list control group and are blinded to the allocation prior to the baseline assessment, and their schools will also not receive information about their allocation. The information letters include information about study content and purpose, but guardians and students were both blinded to the allocation to the intervention or waiting-list control group prior to offering their consent or before the baseline assessment.

### Outcomes

Data will be collected at baseline (T_1_, preintervention) and after approximately 2 weeks of the intervention (T_2_, postintervention) through self-report measures that the adolescents fill in using Nettskjema, a secure online tool to conduct surveys [45]. A follow-up evaluation (T_3_) will be conducted after approximately 3 months to examine if the effects were stable over time.

### Primary Outcomes

Mental health will be assessed with the Strengths and Difficulties Questionnaire (SDQ) [46], the WHO-Five Well-being Index (WHO-5) [47], and the Child and Adolescent Trauma Screen (CATS) [48]. The null hypothesis of this study is that there will not be significant differences in changes in mental health scores between the waiting-list control and the intervention group.

### Secondary Outcomes

How the adolescents cope with cyberbullying will be measured with the Cyberbullying Coping Questionnaire [49]. Help-seeking behavior will be assessed with 3 questions; for example, “Have you told someone about your experiences so they can help you?” Health problems will be assessed using 7 items asking the respondent how often he/she has, for example, experienced headaches. Self-esteem will be measured with the Norwegian Version of the Self-liking and Competence Scale [50,51]. Sleeping quality will be measured with 6 questions (eg, “At what time do you usually go to bed?”) from the Bergen Child Study [52]. Cyberbullying and bullying experiences will be assessed using 4 questions based on the Olweus questionnaire [5].

### Power Calculations

Power calculations were conducted using the software PASS 16 [53]. Using multilevel analysis, it will require a total sample of 400 participants (200 in each group: 20 schools with 20 students per group) to detect an effect size of at least Cohen *d*=0.30, when the expected interclass correlation at school level is 0.01, with a power of 0.79, and a significance level of .05.

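### The cluster layout in the power calculation contradicts itself: 20 schools of 20 students per group makes 400 per group, not the stated 200, and no other section gives the number of schools

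*Protocol article*

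**What the plan says.** The Power Calculations section of the protocol article gives the sample size in one sentence. On the numbers, it calls for "a total sample of 400 participants (200 in each group: 20 schools with 20 students per group". The other inputs are a Cohen d of 0.30, a school-level intraclass correlation ("when the expected interclass correlation at school level is 0.01"), and the operating characteristics "with a power of 0.79, and a significance level of .05". The software is named as PASS 16. The procedure within it, the degrees of freedom and whether the test is one- or two-sided are not given.

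The Randomization section makes the school the unit of allocation, in equal halves: "Half of the schools with the highest value on the random variable will be assigned to the intervention group". It gives no number of schools. The section on eligibility and setting sets a minimum class size of 20 but also gives no number of schools.

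**The concern.** The colon presents the school layout as the make-up of the 200 in each group. Taken that way, 20 schools times 20 students is 400 per group, twice the figure it is meant to explain. Whole schools are allocated to one arm or the other, so a school cannot supply students to both groups, and the 20 schools cannot be shared between them.

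The number of schools matters more here than in an individually randomised trial. It sets the school-level degrees of freedom, the scope for chance imbalance between arms and the recruitment workload. Because this sentence is the only source for that number, someone checking whether recruitment met the plan has to work backwards from the power to guess how many schools were intended.

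**Working it through.** **Inputs, all from Power Calculations:** d = 0.30 (standard deviation set to 1), intraclass correlation 0.01, significance level .05, stated power 0.79, total 400, 200 per group. Equal allocation by school comes from Randomization. **Assumption:** a two-sided test. The article does not say; one-sided is tried below.

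**Step 1: the counts.** 20 × 20 = 400. As worded this is per group, so 2 × 400 = 800 in total, against the printed 200 and 400. With 20 schools in total, half to each arm, the count is 10 × 20 = 200 per group and 400 in total, as printed.

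**Step 2: formulas.** For K schools per group and m students per school:
- design effect DE = 1 + (m − 1) × 0.01
- effective size per group n_eff = K × m / DE
- power ≈ Φ(0.30 × √(n_eff / 2) − 1.96)

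**Step 3: reproduce the stated 0.79.** K = 10, m = 20: DE = 1 + 19 × 0.01 = 1.19; n_eff = 200 / 1.19 = 168.1; 0.30 × √84.03 = 2.750; Φ(2.750 − 1.960) = Φ(0.790) = 0.785. This rounds to the stated 0.79.

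**Step 4: the other layouts.**
- K = 20, m = 20 (literal wording): DE = 1.19; n_eff = 400 / 1.19 = 336.1; power = Φ(3.889 − 1.960) = 0.973.
- K = 20, m = 10 (keeps 200 per group with 20 schools each): DE = 1.09; n_eff = 200 / 1.09 = 183.5; power = Φ(2.873 − 1.960) = 0.820.

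**Step 5: dependence on degrees of freedom.** The same noncentrality is used with a t reference distribution, on either 2Km − 2 (student-level) or 2K − 2 (school-level) degrees of freedom.

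| Schools per group × students | Total students | Normal | t, student df | t, school df |
|---|---|---|---|---|
| 10 × 20 | 400 | 0.785 | 0.783 | 0.739 (18 df) |
| 20 × 20 | 800 | 0.973 | 0.973 | 0.966 (38 df) |
| 20 × 10 | 400 | 0.820 | 0.818 | 0.800 (38 df) |

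**Step 6: one-sided test.** The lowest one-sided power across these three layouts and all three methods is 0.841. A one-sided test therefore does not reproduce 0.79, and the two-sided assumption is the one that fits.

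**The case against.** The strongest reply is that the sentence nearly resolves itself. The total of 400 and the 200 per group agree. Twenty times 20 equals the stated total, and halving 20 schools under the Randomization section gives 10 schools and 200 students per group. That reading keeps every printed number and changes only what the final words of the parenthesis apply to; they may have been meant loosely for the school or class. On this view the fault is one of wording and the design is intact. Most of this stands. What remains is that the same word denotes the trial arm a few words earlier in the same parenthesis, and no other section states how many schools there are.

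Two stronger readings are tempting, and the article does not support them.

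- **A reader might infer that the student target could be 800, or that 400 is wrong.** The printed total, the printed group size and the stated power each rule out 800, since that layout gives about 0.97. The number of students is not in doubt.
- **A reader might infer that 20 schools in total is the only layout that returns 0.79.** That holds under the normal approximation or student-level degrees of freedom. With school-level degrees of freedom, the likely layout falls to 0.74, and 20 schools per group with 10 students each gives 0.80, one point from the stated figure. The article does not say which method was used. The power figure therefore favours 20 schools in total but does not prove it. The main evidence against the 20 × 10 layout is that it replaces a printed 20 with a 10 that appears nowhere as a number of students per school.

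**Conclusion.** The point holds as an error in the stated cluster layout. The only count of randomised units in the article is wrong as written: taken literally it gives 400 students per group against a stated 200, and a power of about 0.97 against a stated 0.79. The total, the group size and the power are consistent with one another and are not challenged.

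The most likely intention is 10 schools per group with 20 students each. This rests on a two-sided test and on a normal approximation or student-level degrees of freedom. If the calculation used school-level degrees of freedom, that layout has power 0.74, so the number of schools and the method behind 0.79 need to be confirmed together. The correction is needed because the figure is relied on for recruitment and appears only once, but under the likely reading the design does not change.

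**What to change.** Check the layout against the PASS output. If it confirms the likely reading, restate the sentence as: 20 schools in total (10 per group), 20 students per school, 200 students per group, 400 in total. If 20 schools per group was meant, correct the students per school and the power to match; with 10 students per school the power is 0.80 to 0.82, depending on the degrees of freedom.

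The cost is one corrected sentence and a look at existing software output. Under the likely reading no further schools or students are needed.

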### Challenges

The intervention and its evaluation have several limitations. First, the intervention may be too comprehensive, aim at too many areas (ie, knowledge, coping, self-esteem, sleep, mental health, and reduce cyberbullying rates), and may partly contain too much information. In particular, the exercise where the adolescent learns about unhelpful or inappropriate thoughts and reframing the situation is long and is based on written information. This might not be appealing to adolescents and that they will therefore not use it. However, it is difficult to redesign this exercise to make it more attractive. Furthermore, we find that the exercise is too important to exclude it from the intervention. The questionnaire to evaluate the intervention is long and may lead to dropping out, response fatigue, or saying no or yes [22]. However, it is necessary to assess these measures to evaluate the effectiveness of the intervention. Both working with the intervention and filling in the questionnaire can be potentially distressing for the adolescents as they are confronted with the seriousness of the cyberbullying event and their thoughts, feelings, and consequences of the event. Therefore, we inform the adolescents about possible contact persons such as school nurses and provide a number to a helpline in the information letter and in the online questionnaire. However, in general, we expect the benefits of the intervention to exceed its disadvantages.

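### The stated power of 0.79 matches a large-sample calculation; with 10 randomised schools per group the same inputs give about 0.74 before any baseline gain

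*Protocol article*

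**What the plan says.** Power Calculations sets the sample size: "it will require a total sample of 400 participants (200 in each group: 20 schools with 20 students per group". The target is a standardised difference of 0.30 or more. The remaining assumptions are put this way: "when the expected interclass correlation at school level is 0.01, with a power of 0.79, and a significance level of .05". The section names the software and a multilevel approach. It does not give the reference distribution, the degrees of freedom, the sidedness of the test, a baseline correlation or an allowance for loss.

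Randomization allocates whole schools: "A random number between 0 and 1 will be generated using SPSS and assigned to each school", and half of the schools go to each group.

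Outcomes sets three measurement times: baseline, about 2 weeks and about 3 months. Planned Statistical Analysis names a linear mixed model with multiple imputation and does not fix a degrees-of-freedom method. Challenges acknowledges that the questionnaire "is long and may lead to dropping out", without a rate.

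**The concern.** In a school-randomised trial the uncertainty of the group contrast is estimated from variation between schools. The design effect accounts for the correlation of pupils within a school. It does not account for that between-school variation being estimated from only 20 schools. A calculation that applies the design effect and then uses a normal reference therefore gives a power that is too high.

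The stated 0.79 is already just under the usual 0.80. If the figure is lower still, a null result read against 79% power for d = 0.30 would be taken as stronger evidence against such an effect than the design supports. Any loss of pupils would lower it further, and the power statement does not say whether the 400 allows for that.

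**Working it through.** **Inputs.** From Power Calculations: d = 0.30 (SD = 1), ICC 0.01, alpha .05, 200 pupils per group, 20 schools, 20 pupils. From Randomization: schools are allocated, half to each group. Assumed: a two-sided test, which is the choice that reproduces 0.79 (one-sided gives 0.866).

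**Layout.** The wording "200 in each group: 20 schools with 20 students per group" can be read in several ways.

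| Reading | Pupils per group | Power, normal | Power, t on school df |
|---|---|---|---|
| 10 schools per group × 20 pupils | 200 | 0.785 | 0.739 (18 df) |
| 20 schools per group × 20 pupils | 400 | 0.973 | 0.966 (38 df) |
| 20 schools per group × 10 pupils | 200 | 0.820 | 0.800 (38 df) |

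Only the first uses both 20s and gives 400 in total. The second gives 800 pupils, and the third contradicts the 20 pupils. None of the t-based figures is 0.79.

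**Step 1: reproduce the plan's figure.**
- Design effect = 1 + (m − 1) × ICC = 1 + 19 × 0.01 = 1.19.
- Effective n per group = 200 / 1.19 = 168.1.
- Noncentrality = d × √(n_eff / 2) = 0.30 × √(168.1 / 2) = 2.750.
- Two-sided normal power = Φ(2.750 − 1.960) = 0.785, which rounds to 0.79. With pupil-level df (398) it is 0.783.

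**Step 2: use school-level degrees of freedom.**
- df = 20 − 2 = 18; critical value 2.101.
- Non-central t with noncentrality 2.750 gives power 0.739. A simulated t-test on school means (200,000 runs) gave 0.740.
- Detectable effect at 79% power: the required noncentrality is 2.925, so d = 2.925 / √(168.1 / 2) = 0.319.

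**Step 3: dependence on the mixed-model test.** The plan names a mixed model, so one with school variance bounded at zero was simulated on the same inputs (complete data, no baseline information).

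| Test | Power | Type I error |
|---|---|---|
| Satterthwaite-type df | 0.73 | 0.043 |
| Fixed 18 df | 0.72 | 0.037 |
| Plain Wald z | 0.77 | 0.051 |

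**Step 4: loss of pupils, if 400 is the number recruited.** The rates are assumptions, since the protocol gives none. Loss is applied as a smaller number per school, with the design effect recomputed and 18 df.

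| Assumed loss | Pupils per school | Effective n per group | Power, 18 df | Power, normal |
|---|---|---|---|---|
| 10% | 18 | 153.8 | 0.70 | 0.75 |
| 20% | 16 | 139.1 | 0.66 | 0.71 |
| 30% | 14 | 123.9 | 0.61 | 0.66 |

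**Step 5: sensitivity to the ICC** (complete data, 18 df): 0.68 at ICC 0.02, 0.62 at 0.03 and 0.53 at 0.05.

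**The case against.** **The 0.79 is not a slip.** It follows from its own inputs under a large-sample reference, and that reference is inferred from agreement at two decimals. This stands. The fault is one of method: the reference does not fit a design with 10 randomised schools per group.

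**The planned analysis may do better than 0.74.** The null hypothesis concerns changes, pupils are measured at baseline, and a mixed model is planned; 0.74 uses none of that. With d on the raw-SD scale and 18 df, baseline adjustment divides the noncentrality by √(1 − r²). A baseline correlation of about 0.34 would restore 0.79 with complete data (2.750 / √(1 − 0.34²) = 2.92), and at 20% loss about 0.52 would be needed. With change scores the divisor is √(2(1 − r)): there is no gain at r = 0.5, and about 0.56 is needed with complete data. This stands as a limit on the conclusion. It does not rescue the stated figure, because the power statement credits no baseline correlation and the protocol gives none.

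**The degrees-of-freedom method is commonly left to the analysis plan.** True, and it changes the size. The simulated plain Wald test reached 0.77 with type I error close to 0.05, so the shortfall could be as small as 2 points. It still does not reach 0.79.

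**A stronger reading does not hold.** A reader might infer that the trial expects dropout, ignores it, and so delivers only 0.66. The documents do not support that. Challenges says only that dropout may occur, no rate is given, and 400 could mean pupils analysed, with the recruitment allowance in the full protocol. A reader might also count the unsourced ICC as a defect; a condensed article commonly leaves out such a source.

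**Conclusion.** The point holds in a limited form. The published 0.79 is too high for the design as described, by about 5 percentage points on a school-level t reference (0.739 against 0.785 before rounding). Across the mixed-model tests simulated, power was 0.72 to 0.77, or 2 to 7 points under the stated 0.79. The effect detectable at 79% power is about 0.32 rather than 0.30.

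This rests on 10 schools per group with 20 pupils each, ICC 0.01, a two-sided test, all 400 pupils analysed, and no credit for baseline or repeated measures. It does not show that the planned model will have less than 79% power, because a moderate baseline correlation could offset the difference. The figures under loss apply only if 400 is the number recruited, and only at the assumed rates.

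**What to change.** Restate the sentence in Power Calculations along these lines: *with 10 schools of 20 pupils per group analysed and school-level degrees of freedom, power for d = 0.30 is about 0.74 without baseline adjustment (ICC 0.01, two-sided alpha .05)*. An equivalent is to state the detectable effect at 79% power as about d = 0.32.

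In the same place:
- Replace the ambiguous bracket with an explicit 10 schools per group.
- Confirm that the test is two-sided.
- Say whether 400 is the number recruited or analysed. If recruited, give power as a conditional range with the loss rates labelled as assumptions (Step 4).

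If the investigators want to claim a gain from baseline measures, they should state the assumed correlation and its basis. A row showing sensitivity to the ICC is optional.

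The cost is a sentence or two and a less favourable headline figure. Enrolment, schools and schedule are unaffected.
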